**Table 1. Metformin dosages adjustment in patients that develop with renal impairment.**

| CKD stage 2-3a
eGFR $\geq$ 60 mL/min | CKD stage 3b
eGFR $\geq$ 45 mL/min | CKD stage 4
eGFR <30 mL/min |
|-----------------------------------------|---------------------------------------|--------------------------------|
| No dose adjustment is needed.           | Reduce dose to 850mg once daily       | Stop                           |

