### **4.3. Justification for Dose**

The recommended starting dose of Metformin hydrochloride tablets for glucose control are 500 mg orally twice a day or 850 mg once a day, given with meals. Diabetes Guidelines recommend dose increments of 500 mg weekly or 850 mg every 2 weeks on the basis of glycaemic control

and tolerability, up to a maximum dose of 2550 mg per day, given in divided doses. Maximum recommended dose is 3 g a day preferably 3 times a day for better tolerability.

The dose used in other antiaging studies range from 1500 to 2000 mg a day. Based on our experience in people with diabetes, we have chosen to start with 850 mg once daily and scale up to 850 mg BID in 4 weeks, as this is the standard and best tolerated dose in terms of gastrointestinal symptoms.

Exceptions will be made in persons receiving dolutegravir who would maintain the 850 mg dose QD due to the pharmacological interaction. Dolutegravir is a known inhibitor of OCT2. Consistent with inhibition of OCT2, co-administration of dolutegravir increased the exposure and decreased the clearance of metformin, an effect that was dose dependent. The magnitude to which dolutegravir increased the exposure to metformin was higher than anticipated (5%) based on the IC50 values for OCT2 (1.9  $\mu$ M), dolutegravir unbound Cmax (twice daily Cmax = 13 mM; free fraction,  $\geq$  1.1%), and the fraction of metformin clearance mediated by active tubular secretion (0.67). Metformin dose will also be adjusted to glomerular filtration rate (See Table 1 Section 6.5)

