### 6.5. Dose Modification

This protocol allows some alteration from the currently outlined dosing schedule, but the maximum daily dose will not exceed.

If there are changes in the antiretroviral treatment, such as starting or stopping dolutegravir, the dose of metformin should be modified accordingly. If dolutegravir is initiated the dose of metformin should be reduced to 850 mg once a day. If dolutegravir is stopped, metformin dosing should be modified to 850 mg dose twice daily.

In those participants that experienced grade 2 gastrointestinal adverse events after metformin dose increase, dose of metformin will be reduced dose to 850 mg once daily.

In case a dose reduction is necessary due to renal impairment, the study intervention will be administered as follows:

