#### **7.1.1. Permanent Discontinuation**

Study medication must be permanently discontinued in the following circumstances:

- Diabetes onset
- Hypersensitivity to the active substance or to any of the excipients.
- Unrecovered severe renal failure (eGFR <45 ml/min).
- Any acute metabolic acidosis event (such as lactic acidosis, diabetic ketoacidosis).
- Adverse events or intolerances related to the study medication, at the investigator's discretion.
- Diagnosis of B or C hepatitis infection or any other progressive liver disease.
- Diagnosis of chronic heart failure, or cancer.
- Alcohol abuse:
  - For men, heavy drinking is typically defined as consuming 15 drinks or more per week.
  - For women, heavy drinking is typically defined as consuming 8 drinks or more per week.
- Participants starting other maintenance medications that according to study drug label are contraindicated with metformin. (Appendix 7)
- Pregnancy.
- Any new events, comorbidities or medications that according to the investigator could entail additional risks for the participant.

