#### **7.1.2. Temporary Discontinuation**

Study medication must be temporary discontinued in the following circumstances:

- Liver laboratory abnormalities: ALT over 5 times the upper limit of normal (ULN) or ALT over 3xULN and bilirubin over 1.5xULN or any verified Grade 4 laboratory abnormality that to the investigators criteria would affect the safety of the participant.

- Acute disorders that involve a risk of impaired kidney function such as dehydration, severe infection, or shock.
- Acute or chronic disease capable of causing tissue hypoxia, such as heart or respiratory failure, recent myocardial infarction, shock, or stroke.
- Hepatic failure, acute alcohol intoxication, alcoholism.
- Study medication should be stopped at the time of surgical intervention with general, spinal, or epidural anesthesia. Treatment can be restarted 48 hours after the intervention surgical procedure or after resumption of oral feeding, provided renal function has been reassessed and proven to be stable.
- Study medication should be stopped prior to or at the time of intravenous iodinated contrast test and should not be restarted until at least 48 hours, provided kidney function has been reassessed.
- Participants unable to swallow study medication tablets during the treatment period.
- Participants starting other temporary medications that according to study drug label are contraindicated with metformin. (Appendix 7)
- Any new events, comorbidities or medications that according to the investigator could entail additional risks for the participant.

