### 7.1.3. Rechallenge

Patients with a permanent or temporary discontinuation will be evaluated by the investigator as soon as possible for safety evaluation and to assess the possibility of re-inclusion.

Rechallenge with the study medication after a temporary discontinuation may be considered at the discretion of the investigator, as long as the event has completely resolved, is not related to the study medication, and the patient agrees to continue the intervention.

In the event of transitory impaired renal function, study medication may be restarted after recovery of an estimated GFR > 45 mL/min.

If the cumulative duration of the interruptions is greater than two months, re-inclusion will not be considered, but study visits will continue as scheduled.

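### Table 1 gives no action for eGFR 30-44 and stops study drug only below 30, while section 7 works with 45 and 7.1.2 lists no eGFR-triggered hold

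*Protocol*

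**What the plan says.** **Dosing rule.** Section 4.3 states: "Metformin dose will also be adjusted to glomerular filtration rate (See Table 1 Section 6.5"). Section 6.5 introduces that table with "In case a dose reduction is necessary due to renal impairment, the study intervention will be administered as follows". Table 1, titled "Metformin dosages adjustment in patients that develop with renal impairment", then has three columns:

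- CKD 2-3a, eGFR at or above 60: dose unchanged.
- CKD 3b, eGFR at or above 45: 850 mg once daily.
- CKD 4, "eGFR <30 mL/min": stop. The cell does not say whether this stop is temporary or permanent.

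**Stopping and restarting.** The permanent list in 7.1.1 includes "Unrecovered severe renal failure (eGFR <45 ml/min"). For transitory renal impairment, 7.1.3 says that "study medication may be restarted after recovery of an estimated GFR > 45 mL/min".

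**Temporary holds.** The renal entry in 7.1.2 is "Acute disorders that involve a risk of impaired kidney function such as dehydration, severe infection, or shock", with no eGFR value. The list ends with a general item: "Any new events, comorbidities or medications that according to the investigator could entail additional risks for the participant".

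**Entry.** Section 5.2 excludes an eGFR below 60.

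**The concern.** The table named as the renal dosing rule and the section that governs discontinuation do not meet. Table 1 is not only a dose-reduction table, because it has its own stop column, and that column begins at 30. Section 7 is built around 45. The word unrecovered in 7.1.1 and the idea of restarting in 7.1.3 make sense only if drug has already been withheld below 45, but 7.1.2, where such a hold belongs, does not list one by eGFR.

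The stake is participant safety. Section 6.6 says that acute renal failure under metformin can lead to lactic acidosis. Table 7 in Appendix 7 gives the same warning for renal dysfunction caused by ACE inhibitors, diuretics and NSAIDs, all of which may be taken with monitoring. An investigator who sees an eGFR in the thirties on a routine panel needs one clear instruction.

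**Working it through.** No sample size, power or error rate is involved. The check is which eGFR values each section covers.

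**Inputs.** Table 1 cut-points 60, 45 and 30 (6.5); permanent-stop value 45 (7.1.1); restart value 45 (7.1.3); no eGFR value (7.1.2); entry limit 60 (5.2). The second column of Table 1 is read as 45-59, since the first column takes 60 and above.

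| eGFR (mL/min) | Table 1, printed values | Section 7 |
|---|---|---|
| 60 or more | No change | No renal action by value |
| 45-59 | 850 mg once daily | No renal stop by value |
| 30-44 | No column | Permanent stop if unrecovered (7.1.1); no eGFR-triggered hold in 7.1.2; no restart until above 45 (7.1.3) |
| Below 30 | Stop | Same as for 30-44 |

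**Width of the gap.** 45 - 30 = 15 mL/min.

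**Distance from the entry limit.**

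- To the stop column of Table 1: 60 - 30 = 30 mL/min, and 30/60 = 50%.
- To the value used in section 7: 60 - 45 = 15 mL/min, and 15/60 = 25%.

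A participant who enters at 60 thus reaches the only stop in Table 1 after a fall of more than 50%. The section 7 value is passed after a fall of more than 25%.

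**Labels.** Stages 3b and 4 follow one another, so the lower end of 3b should meet the upper end of 4. The table sets 3b at 45 or above and 4 below 30, which leaves the same 15 mL/min unassigned. This can be seen from the table alone, without an outside staging scheme.

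**Worked case.** Take a routine panel with eGFR 38, no acute illness, and recovery not yet known.

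1. Table 1 by its printed values: no instruction.
2. Table 1 with the 3b label read down to 30: continue at 850 mg once daily.
3. 7.1.1: stop permanently if unrecovered, which cannot yet be judged.
4. 7.1.2: the acute-disorder entry does not apply; a hold follows only if the investigator sees added risk.
5. 7.1.3: if drug has been held, no restart until eGFR is above 45.

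Steps 1 and 2 disagree. If the value stays at 38, step 2 contradicts step 3.

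**The case against.** **The limits do different jobs.** Table 1 stops outright, 7.1.1 applies only to unrecovered impairment, and 7.1.3 governs restart. They can be read together: stop below 30, stop permanently if below 45 and unrecovered, restart above 45. This stands in part, so it would be too simple to call them two rival limits for one decision. The combined reading still gives no instruction for 30-44 while recovery is unknown, and no text tells the investigator to combine them this way.

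**The gap is partly covered.** 7.1.2 requires a hold for acute disorders that threaten renal function at any eGFR, which takes in common causes of a transient fall. The general item sits under a mandatory heading, so once the investigator sees added risk the hold is required. Both points stand. Neither fixes an action for a fall found only on a laboratory report.

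**A hold may be stated elsewhere.** Appendix 9, on reasons for temporary or definitive discontinuation, was not available. A reader might infer that no part of the protocol states a hold below 45; that cannot be claimed. A hold in Appendix 9 would still leave Table 1 and 7.1.2 out of step with 7.1.1 and 7.1.3.

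**The sponsor may have wanted reduced dosing at 30-44.** The 3b label allows that. Then 7.1.1 and 7.1.3 would be the sections in error, and the protocol would still need correction.

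**Conclusion.** The renal rules are wrong as written and should be fixed. Table 1 leaves 15 mL/min (eGFR 30-44) without an action, places its only stop at 30, and carries labels that do not fit its values. Section 7 relies on 45 without an eGFR-triggered hold in 7.1.2. This rests on the text of 4.3, 6.5 and 7.1.1 to 7.1.3. The protocol does not say how many participants will reach the band; with entry at 60 or more the number is probably small.

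Some stronger conclusions might be inferred, but the document does not support them:

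- **Primary estimate.** The primary analysis set in 9.3 keeps observations after discontinuation, so this is a matter of safety conduct.
- **Exactly 45.** Table 1 doses at 45 and 7.1.3 restarts only above it. A slightly stricter bar for restarting is a legitimate choice.
- **Two-month limit.** In 7.1.3 this caps cumulative interruptions. It does not define unrecovered.
- **Visit spacing.** Long gaps between scheduled panels show no defect here: section 8 allows unscheduled safety samples, and 8.2.3 requires repeats of clinically significant values.
- **Alcohol and heart failure on both lists.** The overlap does not show that one list closes rechallenge and the other leaves it open, because 7.1.3 has re-inclusion assessed after permanent as well as temporary stops.

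**What to change.** 1. Table 1: eGFR 60 or more, no change; 45-59, 850 mg once daily; below 45, stop. Correct the CKD labels to fit these ranges.
2. 7.1.2: add eGFR below 45 mL/min as a temporary hold that becomes permanent under 7.1.1 if unrecovered.
3. Check that Appendix 9 gives the same rule.

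If the sponsor did intend 850 mg once daily at 30-44, it should say so in Table 1 and change 7.1.1 and 7.1.3 instead.

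**Cost.** A protocol amendment with ethics committee approval and, if substantial, health authority approval (10.1.1). There is no new endpoint data and no effect on sample size. The one substantive loss is the reduced-dose band at 30-44, if it was intended; the number of participants concerned is not given.

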### 6.6. Treatment of Overdose

For this study, any dose of metformin greater than three times daily within a 24-hour time period will be considered an overdose.

Summary of product characteristics does not recommend specific treatment for an overdose unless lactic acidosis is developed. A large overdose or concomitant risks of metformin, such as dehydration or acute renal failure, can lead to lactic acidosis. Lactic acidosis is a medical emergency and must be treated in a hospital. The most effective method of removing lactates and metformin is by hemodialysis.

In the event of an overdose, the investigator should:

- Contact the Medical Monitor immediately.
- Evaluate the participant to determine, in consultation with the Medical Monitor, whether study intervention should be interrupted or whether the dose should be reduced.
- Closely monitor the participant for any AE/SAE and laboratory abnormalities until study intervention can no longer be detected systemically (at least 7 days).

- Document the quantity of the excess dose as well as the duration of the overdose.

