### 6.1. Study Intervention(s) Administered

| ARM Name                | Intervention                                                                                                | Control                                                                                                     |
|-------------------------|-------------------------------------------------------------------------------------------------------------|-------------------------------------------------------------------------------------------------------------|
| Intervention Name       | Metformin                                                                                                   | Placebo comparator                                                                                          |
| Type                    | Drug                                                                                                        | Drug                                                                                                        |
| Dose Formulation        | Film-coated tablet                                                                                          | Film-coated tablet                                                                                          |
| Unit Dose Strength(s)   | 850 mg                                                                                                      | N/A                                                                                                         |
| Dosage Level(s)         | One tablet once daily for 4 weeks, followed by one table twice daily                                        | One tablet once daily for 4 weeks, followed by one table twice daily                                        |
| Route of Administration | Oral                                                                                                        | Oral                                                                                                        |
| Use                     | Experimental                                                                                                | Placebo                                                                                                     |

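### Section 6.6 defines overdose by how often metformin is taken and not by how much, so read literally a total above 2,550 mg in three or fewer intakes does not start the overdose actions

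*Protocol*

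**What the plan says.** Protocol section 6.6 gives the only overdose threshold: "any dose of metformin greater than three times daily within a 24-hour time period will be considered an overdose". Meeting it starts a fixed set of actions. The Medical Monitor is contacted at once. Interruption or dose reduction is evaluated jointly. The participant is watched closely for at least 7 days. The size and duration of the excess are recorded.

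The doses around that rule are:

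- Section 6.1, for both arms: "One tablet once daily for 4 weeks, followed by one table twice daily". The active tablet is 850 mg.
- Section 4.3 cites general maxima for metformin: a guideline titration "up to a maximum dose of 2550 mg per day, given in divided doses", and then "Maximum recommended dose is 3 g a day preferably 3 times a day for better tolerability". It does not tie either figure to the overdose rule.
- Some participants are held at one tablet a day. For dolutegravir, section 6.5 says "If dolutegravir is initiated the dose of metformin should be reduced to 850 mg once a day". For reduced eGFR, Table 1 says "Reduce dose to 850mg once daily".

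Section 8 separately asks that urgent safety worries be raised with the sponsor without delay, so that continuing or stopping the drug can be decided.

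**The concern.** An overdose rule is meant to act on the amount taken in a day. This one counts occasions, so two participants with the same 24-hour total can be classified differently because one took it in fewer sittings. A participant who doubles up at each of two intakes passes the literal test.

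What is at stake is whether the section 6.6 actions start by rule or only because the investigator thinks they should. The section itself notes that a large overdose can lead to lactic acidosis. Appendix 4 does not fill the gap for an accidental excess without symptoms: an overdose as such is reported as an adverse event only if intentional with possible self-harm, and otherwise only its signs, symptoms or sequelae are.

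**Working it through.** **Inputs.** Tablet strength 850 mg (6.1). Trigger: more than three times in 24 hours (6.6). Cited maxima: 2,550 mg and 3,000 mg per day (4.3). Assigned dose: 850 mg/day (one tablet) or 1,700 mg/day (two tablets).

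**Formula.** 24-hour total = intakes × tablets per intake × 850 mg.

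**The protocol's own figure first.** 3 × 850 = 2,550 mg, which equals the guideline maximum in 4.3. At one tablet per intake, three intakes (2,550 mg) pass and four (4 × 850 = 3,400 mg) are caught. In that case the rule and the maximum agree.

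**More than one tablet per intake.** The sentence can be read in three ways: more than three intakes (literal), more than three tablets (probably intended), or more than three times the prescribed daily dose.

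| Assigned per day | Intakes × tablets | Total | Multiple of assigned dose | >3 intakes | >3 tablets | >3 × daily dose |
|---|---|---|---|---|---|---|
| 2 tablets | 4 × 1 | 3,400 mg | 2.0 | caught | caught | missed |
| 2 tablets | 2 × 2 | 3,400 mg | 2.0 | missed | caught | missed |
| 2 tablets | 3 × 2 | 5,100 mg | 3.0 | missed | caught | missed |
| 2 tablets | 3 × 3 | 7,650 mg | 4.5 | missed | caught | caught |
| 1 tablet | 3 × 1 | 2,550 mg | 3.0 | missed | missed | missed |

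**Size of the smallest example.** Four tablets in two intakes: 3,400 / 2,550 = 1.33 and 3,400 / 3,000 = 1.13. It exceeds both maxima in 4.3, so the choice between them does not matter with this tablet. Rows one and two show the inconsistency: the same 3,400 mg is caught or missed depending only on the number of intakes.

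**Participants held at one tablet.** Three tablets are 2,550 / 850 = 3.0 times the assigned dose and trigger nothing under any of the three readings. The total does not exceed either maximum in 4.3.

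**The case against.** The best defence is that the wording is awkward English for more than three tablets. Every scheduled intake is one tablet, and section 6.6 asks for the quantity of the excess, so a total was evidently intended. A sensible investigator told of four tablets in two intakes would treat it as an overdose. Section 8 offers immediate escalation to the sponsor that needs neither symptoms nor a threshold. In practice few cases would surface. After week 24 the visits are 24 weeks apart, and a pill count cannot reveal a 24-hour total.

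Most of this stands, and it keeps the point small. It does not remove it. An operative safety threshold should say what it means, and section 8 relies on judgement and does not require the 7 days of monitoring.

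A reader might infer three stronger things that the documents do not support:

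- **That one cut-off for all regimens is an error.** Section 4.3 does say that "co-administration of dolutegravir increased the exposure and decreased the clearance of metformin", and three tablets do not trigger section 6.6 in participants held at one. But nothing in the protocol requires an overdose limit relative to the assigned dose, 2,550 mg exceeds neither cited maximum, and no lower figure has a source in the document. A single absolute threshold is a legitimate choice.
- **That section 6.5 confirms there is no cap.** Its sentence ends at "but the maximum daily dose will not exceed" in the text available. A figure may have been lost in extraction or redaction, so the sentence carries no weight here.
- **That participants are exposed to a known harm.** The size of the dolutegravir interaction is not given, so no exposure or risk can be calculated.

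**Conclusion.** The point holds in a limited form. As written, the overdose trigger is a frequency. It agrees with the 2,550 mg maximum at one tablet per intake, but it does not catch a larger total taken in three or fewer intakes, the smallest example being 3,400 mg in two intakes. In that case the section 6.6 actions rest on the investigator's judgement and not on the rule.

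This assumes a literal reading of the sentence and the 850 mg tablet. If the sentence is read as more than three tablets, the gap closes and only the wording needs correcting. Whether participants restricted to one tablet need a lower threshold is a clinical decision for the sponsor and not a demonstrated error. No endpoint, sample size or analysis is touched. Minor: worth correcting because it is an operative safety rule and the correction is almost free.

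**What to change.** Restate the definition in section 6.6 as: *more than three tablets of study medication (more than 2,550 mg if metformin) in total within any 24 hours, however split*. Counting tablets lets a blinded investigator apply it to either arm, and it removes the three competing readings.

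Optionally, the sponsor's clinicians could consider a lower tablet count for participants held at one daily because of dolutegravir or reduced eGFR. The protocol gives no basis for a specific figure, so any number would need clinical justification.

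The cost is one sentence and at most a few more Medical Monitor contacts.
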